# Exercise program to reduce the risk of cognitive decline and physical frailty in older adults: study protocol for an open label double-arm clinical trial

**DOI:** 10.3389/fnagi.2023.1162765

**Published:** 2023-05-19

**Keywords:** older adults, physical exercise, cognitive decline, physical frailty, mild cognitive impairment

## Abstract

**Objective:**

It is a big problem that many older adults are physically inactive. Well-known benefits of physical exercise include a decrease in the risk of cognitive decline and physical frailty. Therefore, this study aims to examine whether our proposed exercise program can prevent cognitive decline and improve physical function in the elderly.

**Methods:**

This study will include nondemented older adults (*n* = 160) without regular exercise habits. The trial will include a physical exercise training program (once a week) and nutritional lectures (once a month) over 5 months and follow-up for ≥1 year. The primary endpoint is the program’s efficacy in preventing cognitive decline, as assessed by changes in the memory performance index of the mild cognitive impairment (MCI) screen; the secondary endpoints are the incidence of MCI and dementia, physical testing, and frailty proportion. In the exploratory phase of the study, we will elucidate the underlying diseases causing MCI in community-dwelling older adults by neuroimaging.

**Discussion:**

This double-arm trial that aims to assess the impact of physical exercise on nondemented older adults’ cognitive and physical function. Furthermore, our newly developed exercise program will be easy for older adults to undertake.

**Clinical Trial Registration**: https://clinicaltrials.gov/, identifier [jRCT 1040220140].

## Introduction

1.

Alzheimer’s disease (AD) disease-modifying therapy can be useful, particularly during the mild cognitive impairment (MCI) and preclinical stages. Additionally, nonpharmacological approaches to MCI, such as lifestyle-based dementia prevention programs, including exercise and nutrition, can be efficacious for preventing or delaying the onset of dementia (Ngandu et al., 2015); to this end, early detection of MCI is essential. The prevalence of MCI among community-dwelling older adults has been reported at 17.0% (Ninomiya et al., 2020); however, the underlying diseases causing MCI are not sufficiently known because most patients with MCI do not go to the hospital or undergo either magnetic resonance imaging (MRI) or detailed cognitive tests.

Many older adults are physically inactive (Lee et al., 2012), although the health benefits of physical activity are well-known (World Health Organization, 2022). Physical exercise has been reported to reduce the risk of cognitive decline and physical frailty in older adults (Erickson et al., 2011; Cadore et al., 2014; Kulmala et al., 2014). In Japan, fractures and joint diseases, as well as dementia, are the two major diseases requiring nursing care for the elderly. If older adults would do a physical exercise routine, the number of older adults in long-term nursing care could decrease. However, in this country, only 44.4% of men and 37.1% of women ≥75 years old reported having a physical exercise routine (Cabinet Office, 2020). Therefore, an exercise program that would help older adults engage in a physical exercise routine is necessary.

Recently, we started a project for better diagnosing and preventing MCI among community-dwelling adults. A 10-min self-administered, electronically scored test called MCI screen (Cho et al., 2008; Shankle et al., 2009) is used to detect patients with MCI among nondemented elderly people. With respect to preventing dementia, we developed a physical exercise training program which is easy to start and continue for older adults, including multitasking, resistance, and aerobic exercises. We want to examine if the exercise program can reduce the risks of cognitive decline and physical frailty in this population.

The aims of this study are to examine whether the exercise program (i) can prevent cognitive decline and (ii) improve physical function and to elucidate the underlying diseases resulting in MCI among community-dwelling older adults.

## Methods and analysis

2.

### Study design

2.1.

Nondemented older adults, including those with MCI (≥65 years) who do not have regular exercise habits will be recruited via local advertisements in Hakusan-city, Ishikawa Prefecture, Japan. This is an open label 1-year double-arm study that will be conducted in geriatric clinics and senior day care center in Japan. Figure 1 illustrates the study’s time course and Figure 2 shows flow chart of participants. Older adults will undergo the MCI screen which is used to detect patients with MCI, and all subjects with scores both above and below the cutoff of MCI screen except for subjects with dementia will be encouraged to participate in exercise classes.

**Figure 1 fig1:**
[figure not shown]
Study time course.

**Figure 2 fig2:**
[figure not shown]
Flow chart of participants.

### Inclusion and exclusion criteria

2.2.

The only inclusion criterium is age ≥ 65 years. The exclusion criteria include the following: (i) prohibition from exercising by a medical doctor, (ii) a diagnosis of dementia, and (iii) a nursing care level of the long-term care insurance (LTCI). In Japan, LTCI is a mandatory social insurance program that assists disabled older adults with daily living activities (Tamiya et al., 2011).

### Intervention program

2.3.

#### Physical exercise training program

2.3.1.

The intervention comprises individually tailored exercises, including multitasking, resistance, and aerobic exercises (Table 1). All training will be conducted at the gym once a week and guided by exercise therapists during the first 5 months. The resistance exercise program is standardized to include exercises for the six main muscle groups (quadriceps femoris muscle, hamstring muscle, latissimus dorsi and arm muscles, and abdominal and back muscles). The aerobic exercise program can be either cycling on an ergometer or treadmill running. The complete training program is supervised by professors of exercise physiology and exercise therapists.

**Table 1 tab1:** Physical exercise training program.

Multitask exercise		
	Exercise frequency per week	1
	Exercise duration (min)	15
Resistance exercise		
	Exercise frequency per week	1
	Exercise duration (min)	20
Aerobic exercise		
	Exercise frequency per week	1
	Exercise duration (min)	30

#### Nutritional lectures

2.3.2.

All participants will attend lectures on the principles of a healthy diet once a month during the first 5 months provided by the study nutritionist. The nutritionist will teach about a low-salt diet, diet to prevent diabetes and dyslipidemia, and protein intake to prevent frailty. Questionnaire on eating habit is obtained to assess the adherence to the proposal diet at baseline, the 5-month and 1-year follow-ups.

### Screening, baseline, follow-up, and outcome measurements

2.4.

Data will be obtained at four different times: at screening, at baseline, at the 5-month and 1-year follow-ups. The schedule for the variables to be measured is shown in Table 2. Cognitive test (MCI screen), physical test, body composition, questionnaire on nutrition/medical history/regular exercise will be performed at screening or at baseline and 5 months later. Additionally, the MCI screen, questionnaire on medical history/regular exercise will be obtained at 1-year visit.

**Table 2 tab2:** Schedule for the participants of the study.

	SC	Baseline	5-month	1-year
MCI screen	●		●	●
Physical test		●	●	
Body composition		●	●	
Nutrition questionnaire		●	●	
Questionnaire on medical history	●		●	●
Questionnaire on regular exercise		●	●	●

#### Primary outcome measures

2.4.1.

The primary outcome is the program’s efficacy in preventing cognitive decline, as assessed by changes in the memory performance index (MPI) scores of the MCI screen between the screening and 5-month and 1-year follow ups. We will compare between exercise participants and nonparticipants.

#### Secondary outcome measures

2.4.2.

Secondary outcomes include (i) the proportion of people who exercise regularly, (ii) the incidence of MCI and dementia at 1-year follow-up, (iii) changes in physical tests, (iv) body composition, and (v) the proportion of people who are frail and prefrail.

#### Exploratory examination

2.4.3.

For participants whose MPI is below the cutoff score at the screening or follow-up, a mini-mental state examination-Japanese (MMSE-J), brain MRI, ^123^I-iodoamphetamine (IMP)-cerebral blood flow single photon emission computed tomography (SPECT), and blood chemistry analysis [hemoglobinA1c, thyroid hormone, *Treponema pallidum* (TP) antigen STS test, TP antibody LA test, folic acid, vitamins B1 and B12] will be performed to elucidate the underlying disease of cognitive decline. Furthermore, subjects relevant to ≥1 of the following items are recommended for additional examinations: (i) low scores on the MMSE-J (<26 points) or zero points in the delayed recall sub-item, (ii) abnormality of disease-specific region on ^123^I-IMP-SPECT, such as the posterior cingulate, precuneus, and occipital lobe, (iii) hippocampal atrophy (>1.8 on the Voxel-based Specific Regional analysis system for Alzheimer’s Disease: VSRAD), (iv) severe leukoaraiosis. The additional examinations will include the Wechsler Memory Scale-Revised (WMS-R), ^11^C-Pittsburgh compound-B (PiB)-positoron emission tomography (PET), and ^18^F-fluorodeoxyglucose (FDG)-PET to diagnose the underlying diseases, including AD, vascular dementia (VaD), and Dementia with Lewy bodies (DLB).

We will investigate the relationships between program’s efficacy on cognitive function and amyloid pathology (positive or negative of PiB-PET) or arteriosclerotic factors (hypertension, diabetes mellitus, and dyslipidemia). We will also explore the association between the results of various examination such as brain MRI, ^123^I-IMP-SPECT, ^11^C-PiB, and ^18^F-FDG-PET and the progression of cognitive decline.

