The novelty of our study is to examine whether the exercise program is able to reduce the risk of cognitive decline in older adults with MCI due to AD according to biomarkers. We will investigate the association between AD biomarkers and progression of cognitive decline in this trial. High levels of cerebrospinal fluid (CSF) total tau levels and low levels of CSF amyloid-β_1–42_ were reported to be predictors of rapid cognitive decline in AD (Koch et al., 2013). In the Amyloid Tau Neurodegeneration (ATN) framework, amyloid positive in PiB-PET and low levels of CSF amyloid-β_1–42_ are amyloid markers, and AD findings of FDG-PET and hippocampal atrophy in MRI as well as high levels of CSF total tau are neurodegeneration markers. It was also reported the potential link between atherosclerosis and amyloid metabolism (Martorana et al., 2015). We will clarify the association between amyloid pathology, the presence of arteriosclerotic factors, and the exercise program’s efficacy in cognition.

A major limitation of this study is its nonrandomized control design. However, we hope to demonstrate that starting and continuing physical exercise can prevent cognitive decline and improve physical function in older adults. Additionally, we will elucidate the proportion of MCI due to AD with amyloid biomarker among community-dwelling older adults with MCI.

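### Amyloid PET reaches only triaged low scorers, so the scanned share does not estimate the AD proportion of community MCI, and follow-up-triggered scans would distort the exploratory amyloid-by-efficacy analysis

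*Protocol article*

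**What the plan says.** Access to PiB-PET passes through two steps, both in section 2.4.3 (Exploratory examination). The first is an MPI score under the cutoff, which section 2.4.4 sets at 50.2: the work-up is done "For participants whose MPI is below the cutoff score at the screening or follow-up". The second is triage: "subjects relevant to ≥1 of the following items are recommended for additional examinations". The items are a low MMSE-J or zero delayed recall, a disease-pattern SPECT abnormality, hippocampal atrophy, and severe leukoaraiosis. PiB-PET is one of the additional examinations, so it comes only after both steps, and then as a recommendation.

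The same section plans to relate the programme's "efficacy on cognitive function and amyloid pathology", with amyloid status read from PiB-PET. Section 2.4.1 measures efficacy as "changes in the memory performance index (MPI) scores of the MCI screen between the screening and 5-month and 1-year follow ups".

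Section 2.4.5 defines MCI by Petersen's criteria, which are separate from the triage items. The Discussion (section 3) then says that "we will elucidate the proportion of MCI due to AD with amyloid biomarker among community-dwelling older adults with MCI". It also presents as the study's novelty whether the programme can "reduce the risk of cognitive decline in older adults with MCI due to AD according to biomarkers".

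**The concern.** The people with a known amyloid status are not a sample of community MCI. They scored low and then showed a further abnormality. Hippocampal atrophy and posterior cingulate or precuneus hypoperfusion point towards AD, so scanning is more likely where amyloid is more likely. This is partial verification, and the share among the scanned answers a different question from the one the Discussion poses.

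Separately, one of the two entry routes depends on the follow-up value of the variable that measures efficacy. A person who enters only at follow-up was at or above 50.2 at screening and below it later, so that person's MPI fell by construction. If exercise works, fewer exercisers than nonparticipants enter this way. The nonparticipant side of the scanned set is then enriched with decliners, and the arms are no longer comparable within it.

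At stake are a proportion promised without qualification and a biomarker-defined effect presented as the novelty of the study.

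**Working it through.** **The plan's own figure.** Section 2.6 uses d = 0.5, α = 5% and 80% power. The normal approximation gives 2(1.96 + 0.84)²/0.5² ≈ 63 per group, and the noncentral t gives 64 (power 80.1%). Then 128/0.8 = 160. The stated size reproduces. The article states no size for the PiB-PET analyses.

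**Step 1: bounds on the AD share.** Let f be the fraction of MCI cases scanned and q the positive share among them. The unscanned may be all negative or all positive, so the share among all MCI lies between f·q and f·q + (1 − f). The article gives neither f nor q. With q = 0.6 assumed:

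| f (assumed) | lower | upper |
|---|---|---|
| 0.5 | 0.30 | 0.30 + 0.50 = 0.80 |
| 0.7 | 0.42 | 0.42 + 0.30 = 0.72 |
| 0.9 | 0.54 | 0.54 + 0.10 = 0.64 |

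The width is 1 − f whatever q is. Sampling error comes on top.

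**Step 2: direction.** Suppose 46.6% of low scorers are amyloid-positive and triage passes 80% of positives and 40% of negatives (all assumed). The share among those passing is 0.466·0.8 / (0.466·0.8 + 0.534·0.4) = 0.373/0.586 ≈ 64%, against a true 47%.

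**Step 3: selection on the outcome.** This was simulated with equal true benefit for everyone and comparable arms. The true effect is 0.5 SD of change, which is 0.5·√(2(1 − ρ)) in units of the screening SD, where ρ is the visit correlation. With 17% below the cutoff at screening, before triage:

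| ρ (assumed) | true | screening or follow-up route | ratio |
|---|---|---|---|
| 0.6 | 0.447 | 0.710 | 1.59 |
| 0.7 | 0.387 | 0.578 | 1.49 |
| 0.8 | 0.316 | 0.439 | 1.39 |

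At ρ = 0.7 the screening-triggered set alone gives 0.388. Follow-up-only entry is 3.1% of exercisers against 7.9% of nonparticipants. With no true effect the inflation is about 0.

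Adding triage (80% and 40%, as above), 30% amyloid-positive overall, amyloid-positive people 0.5 SD lower at screening with a further 0.3 SD shortfall at follow-up, and no true interaction:

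| ρ | low at screening | true | screening route | either route, amyloid + | either route, amyloid − | spurious interaction |
|---|---|---|---|---|---|---|
| 0.6 | 17% | 0.447 | 0.445 | 0.622 | 0.735 | −0.113 |
| 0.6 | 30% | 0.447 | 0.449 | 0.563 | 0.653 | −0.090 |
| 0.8 | 17% | 0.316 | 0.313 | 0.392 | 0.455 | −0.063 |
| 0.8 | 30% | 0.316 | 0.314 | 0.371 | 0.411 | −0.040 |

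The effect is overstated in both strata in every scenario, and the interaction moves little. Varying the assumed amyloid deficit from 0 to 1 SD took the interaction from about 0 to −0.18.

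**Step 4: numbers per cell.** The Introduction cites an MCI prevalence of 17%. Taking that as the fraction below the cutoff (an assumption), 0.17·160 ≈ 27 people at screening and 0.17·128 ≈ 22 completers, so 22/4 ≈ 5.4 per arm-by-amyloid cell if all are scanned and split evenly. Adding follow-up entries at ρ = 0.7 gives 17% + (3.1% + 7.9%)/2 = 22.5%. Then 0.225·128 = 28.8, or 7.2 per cell. If only 50% to 90% of the 22 are scanned, the count is 11 to 20, about 3 to 5 per cell.

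The interaction detectable at 80% power is about 2.8·√(4/n) SD of change: 2.4 SD at n = 5.5 and 2.1 SD at n = 7.2. The planning value for the main comparison is 0.5.

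**The case against.** The strongest reply is that section 2.4.3 says who is worked up, not who is analysed. It nowhere says that screening-triggered and follow-up-triggered scans will be pooled, and an article may leave the population of an exploratory subgroup to a fuller document. That stands: pooling is the natural reading but an unstated one, so the second part of this point is conditional on it. The first part is not conditional, because the gating rule and the target population of the proportion are both stated and they do not match.

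A reader might also infer more than the documents support:

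- That the planned amyloid contrast is about half again too large. The 0.39 to 0.58 SD inflation concerns the exercise effect inside the selected set. The contrast between amyloid strata shifts far less, and by little beside what these numbers could detect.
- That the plan counts unscanned people as amyloid-negative. It fixes no handling of them.
- That amyloid-by-efficacy is a named aim. The Introduction names cognition, physical function and the diseases underlying MCI. The amyloid-by-efficacy analysis appears under the exploratory heading and in the Discussion, with no power claimed.
- That 30–80% is the uncertainty. It is the result at one assumed scan rate. With four alternative triage items the rate could be high, and at 90% the range is 54–64%.
- That a screening-triggered subset would be unbiased. That held in a simulation with comparable arms. The Discussion itself names the nonrandomized design as a major limitation.

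The exploratory label lowers the weight of the point. It does not remove it, since the Discussion promises the proportion outright and puts the biomarker-defined effect forward as the novelty.

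**Conclusion.** The point holds in three parts.

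1. The scanned share does not estimate the AD proportion among community-dwelling MCI and is likely too high, because several triage items track AD. The proportion is not beyond reach: it can be bounded for all MCI, or reported for the triaged subset as such. How wide the bounds are depends on the unknown scan rate.
2. If follow-up-triggered scans enter the amyloid-by-efficacy analysis and exercise has an effect, the effect is overstated within each amyloid stratum, with a small spurious interaction possible. The direction follows from the entry rule. The sizes rest on the assumed visit correlation, triage rates and amyloid deficit.
3. With at best about 5 to 7 completers per cell, the subset cannot carry a claim about efficacy in MCI due to AD.

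The primary comparison and its sample size are untouched.

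**What to change.** - Report the AD proportion with all Petersen-defined MCI as the denominator. Give the number scanned and the lower and upper bounds for the unscanned, and label the scanned-only figure as conditional on low MPI and triage.
- Base the amyloid-by-efficacy analysis on people whose work-up was triggered at screening, and describe follow-up-triggered scans separately. State that this removes selection on the outcome but not confounding from the nonrandomized arms.
- Reword the two Discussion sentences, so that the novelty claim is descriptive and hypothesis-generating and the proportion names the population it refers to.

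The cost is a somewhat smaller exploratory subset and a weaker claim. No extra scans are needed, and the primary analysis does not change.

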#### MCI screen

2.4.4.

The MCI screen requires 10 min; the MPI quantifies the pattern of recalled and nonrecalled words on a 0–100 scale, with lower scores indicating worsening cognition. It can distinguish healthy people from MCI with 96–97% accuracy (Shankle et al., 2009). We used a cutoff point of 50.2 to distinguish MCI.

#### Diagnosis of MCI, dementia and its subtypes

2.4.5.

MCI is defined by Petersen’s criteria (Petersen et al., 2001), and dementia is diagnosed according to the major neurocognitive disorder of Diagnostic and Statistical Manual of Mental Disorders, Fifth Edition (DSM-5) (American Psychiatric Association, 2013). In addition, to precisely diagnose MCI due to AD and AD dementia, we will use the National Institute on Aging and Alzheimer’s Association research framework (Jack et al., 2018). The diagnosis of other dementia subtypes will be made based on the National Institute of Neurological Disorders and Stroke-Association International pour la Recherche et I’Enseignement en Neurosciences criteria (Román et al., 1993) for VaD and the Fourth Consensus Report of the Dementia with Lewy Bodies Consortium (McKeith et al., 2017) for DLB. Clinical information, including neuroimaging findings, will be used for AD, VaD, and DLB diagnosis. Expert neurologists in the study team will adjudicate every case of dementia.

### Assessment of physical frailty

2.5.

Physical frailty and its phenotype will be assessed according to Fried criteria and the revised Japanese version of the Cardiovascular Health Study criteria (revised J-CHS criteria) (Fried et al., 2001; Satake and Arai, 2020), namely, weight loss, slowness, weakness, exhaustion, and low physical activity.

### Sample size and statistical considerations

2.6.

Assuming an alpha error of 5% (*α* = 5%) and a difference between intervention participants and nonparticipants groups exercise program values of *d* = 0.5, the required sample size for an 80% power is 64 participants per group. Considering a 20% expected loss to follow-up, the final sample size should be 160.

For comparisons between baseline and follow-up, repeated measures ANOVA will be used. The level of statistical significance will be 0.05. Data will be analyzed using the Statistical Package for the Social Sciences software (version 28; SPSS Inc., Chicago, IL, United States).

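### Repeated measures ANOVA, if fitted as one model over the three MPI visits, discards observed MPI values from people later lost, and biases the group comparison if decline-related dropout differs between participants and nonparticipants

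*Protocol article*

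**What the plan says.** The Primary outcome measures section defines the outcome as "changes in the memory performance index (MPI) scores of the MCI screen between the screening and 5-month and 1-year follow ups", compared between exercise participants and nonparticipants. Table 2 confirms that the MCI screen is given at those three visits.

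The Sample size and statistical considerations section gives the planning figures: "the required sample size for an 80% power is 64 participants per group", and then "Considering a 20% expected loss to follow-up, the final sample size should be 160". The only analysis it names is "For comparisons between baseline and follow-up, repeated measures ANOVA will be used", to be run in SPSS version 28. The article mentions no mixed model, imputation or other treatment of incomplete MPI.

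Study design describes the trial as open label, and the Discussion names the nonrandomised control design as a major limitation.

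**The concern.** Classical repeated measures ANOVA, as in the SPSS repeated-measures general linear model, removes any participant with a missing value at a modelled visit. With three MPI visits in one model, someone seen at screening and 5 months but absent at 1 year contributes nothing, even to the 5-month comparison for which the value exists.

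The enlarged sample covers this loss in number, not in selection. One group attends a supervised weekly class and the other does not, everyone knows which group they are in, and people with MCI are eligible. Reasons for leaving could therefore differ between the groups and could depend on how the person is doing. If people who decline leave the program group more readily, those who remain make the program look better than it is. If they leave the nonparticipant group more readily, a real benefit is understated.

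**Working it through.** **1. The plan's own figure.** Inputs from the sample size section: alpha 5%, d = 0.5, power 80%, loss 20%. A two-sided two-sample t-test needs 63.77, so 64 per group. Then 2 × 64 = 128, and 128 / (1 − 0.20) = 160. The stated figure reproduces. Since 160 × 0.80 = 128, the planned power already assumes a completers-only analysis.

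**2. Data discarded.** Expected losses are 160 × 0.20 = 32. All 32 lose their screening MPI from a three-visit ANOVA. A 5-month value is lost only for those who leave after month 5. The article gives no timing, so let s be the share of losses after month 5. The number with an observed 5-month MPI is 160 − 32(1 − s), against 128 in the ANOVA whatever s is. Power below is for a two-sided t-test at d = 0.5 on everyone observed at 5 months, split equally.

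| s | 5-month MPI discarded by ANOVA | Observed at 5 months | Power |
|---|---|---|---|
| 0 | 0 | 128 | 80.1% |
| 0.5 | 16 | 144 | 84.6% |
| 1 | 32 | 160 | 88.2% |

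**3. Bias in the group comparison.** The document gives no dropout pattern, so everything here is assumed. The simulation used three visits with unit SD and equal correlation rho, and no true effect. Dropout was 20% per group, all after month 5. In the program group the log-odds of leaving rose by b per SD of 5-month decline; in nonparticipants loss was random. Change is scaled by its SD, √(2(1 − rho)). Results for rho of 0.6 and 0.8 were nearly identical:

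| b | Complete cases, 5 months | Complete cases, 1 year | All observed MPI, 1 year |
|---|---|---|---|
| 0.7 | 0.13 | 0.06 to 0.07 | about 0 |
| 1.0 | 0.17 | 0.09 | about 0 |
| 1.4 | 0.22 | 0.11 | about 0 |

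If d = 0.5 is read in SD of change, the 5-month error is 0.13/0.5 = 26% to 0.22/0.5 = 44% of the planned effect.

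**4. When the bias vanishes or reverses.** These runs used rho of 0.5 and 0.7 and, where loss was linked to decline, b = 1.
- Random loss in both groups: no bias.
- Same decline-related mechanism and 20% rate in both groups: each group's mean change is too favourable by about 0.17 SD at 5 months and 0.09 SD at 1 year, but the errors cancel. A true difference of 0.50 is estimated as 0.50.
- Decline-related loss in one group only, or the same slope with 10% against 30% loss: a true 0.50 becomes about 0.33 to 0.67 at 5 months and 0.41 to 0.59 at 1 year, in either direction.

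**5. Limits of the remedy.** Step 3 makes dropout depend on an observed value, which is missing at random, so a likelihood estimate is unbiased by construction. If one-arm dropout instead follows the unobserved 1-year decline (b from 0.7 to 1.4, rho 0.6 and 0.8), complete cases are biased by 0.13 to 0.22 SD at 1 year. The estimate from all observed MPI is still biased by 0.09 to 0.17 SD.

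**The case against.** The strongest objection is that the article does not fix one three-visit model. The ANOVA sentence refers to comparisons of baseline with follow-up and covers all outcomes, some of which have only two visits. Two separate analyses, screening to 5 months and screening to 1 year, would fit that wording and keep every 5-month value. This stands as a condition on the point. One model is the natural reading of an outcome defined by change "between the screening and 5-month and 1-year follow ups", but it is not stated. Even with separate analyses, the 1-year comparison would use only those who returned.

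It can also be said that missing-data handling belongs in an analysis plan not shown here. That would answer a complaint about absent detail. The point here concerns the method that the article does name, together with a loss that it expects.

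A reader might infer that all 20% forfeit both a screening and a 5-month value, and that decline-related dropout necessarily biases both time points. The document supports neither. People who leave before month 5 have no 5-month value to discard, and equal decline-related dropout in both groups leaves the contrast unbiased. Nothing in the article shows that dropout will differ.

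Finally, a simulation with dropout tied to observed decline favours a mixed model. That is correct; step 5 shows that most of the bias remains when dropout follows unobserved decline.

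**Conclusion.** The point holds conditionally. The loss of observed 5-month data requires a single three-visit model and losses after month 5. Bias in the primary contrast also requires dropout related to decline that differs between the groups, in mechanism or in rate. The open-label, nonrandomised design makes that plausible but does not establish it.

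The false benefits in step 3 rest wholly on the assumed one-arm pattern. In that scenario the 5-month error is entirely avoidable, because every 5-month value was observed. Planned power is not at issue. This should be changed before MPI outcomes are analysed, since a better method is available with the same data and software, but it does not invalidate the design.

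**What to change.** In the statistical section, for MPI only, replace repeated measures ANOVA with a linear mixed model for repeated measures: group, visit and group-by-visit terms, unstructured covariance, every observed MPI value included. State that it is valid under missing at random. Add a sensitivity analysis for dropout that depends on unobserved decline, for example a delta-adjusted analysis with the shift varied by group, and keep the complete-case ANOVA as a secondary check.

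The cost is a sentence or two of text and slightly more analysis work. The sample size, visits and data are unchanged, and SPSS version 28 fits the model. The change does not remove confounding from the nonrandomised comparison, which needs separate treatment.
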